### 2.4. Recruitment and Sample Size Considerations

Recruitment will occur through the University of Calgary social media and research sites. We anticipate that a snowball sampling effect will also occur. Interested participants will be contacted by a research assistant to complete an online survey to ensure they meet the inclusion criteria (Table 1 and Table 2).

Previous ultrasound studies validating urine hormone monitor measurements have targeted 50 participants over 3 cycles, for a total of 150 menstrual cycles [41]. With 150 cycles for analysis, the study would be adequately powered to detect differences of 0.5 days in the estimated day of ovulation, cycle length, and follicular/luteal phase lengths. This calculation was done with G*Power 3.1, with an effect size of 0.2, alpha 0.05, and power of 80%. This calculation is valid for correlation statistics with an a priori power analysis with one tail. Oversampling up to 60 participants may be required to ensure that we have 150 cycles for analysis. The same sample size will be used for recruitment of the PCOS and athlete groups. We know that the participant burden is high, and therefore, we are prepared to continue to recruit until we reach sample size.

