## 3. Results (Planned)

### 3.1. Data Analysis

Datasets will be analyzed using SPSS version 29 (IBM, Chicago, IL, USA) and charts prepared using SPSS or Excel (Microsoft, Redmond, WA, USA). Descriptive statistics will be used to determine the means, standard deviations (SD), and 95% confidence intervals (CI) of the menstrual cycle parameters, i.e., cycle length, day of ovulation, length of the follicular phase and the luteal phase, menstrual bleeding scores, and duration. The ultrasound-defined day of ovulation (US-DO) will be considered day 0 as a reference for days leading up to and after ovulation. The main analysis in this sample (for which it is powered) will be to correlate (with Spearman’s correlation coefficients) the day of ovulation with peak levels of LH on the Mira monitor, as well as with the day of progesterone elevation, to confirm ovulation. Sensitivity and specificity analyses of each hormone in relation to the US-DO will be calculated.

Secondary exploratory data analyses (not considered in the power calculations) will include daily average hormone values from the Mira monitor referenced to day 0 (US-DO), average hormone values, 95% confidence individuals on days leading up to ovulation (days −5, −4, −3, −2, −1, etc.), and after ovulation (days +1, +2, +3, +4, +5 etc.) from cycle day 6 until the end of the cycle. Daily means, SDs, and CIs of hormone values across the study sample will be used to describe the variability in the population, as was done in the pilot study [34], and individual (personalized) hormone patterns will also be considered as we have presented in previous studies [51]. Day-to-day hormone variability will require complex modelling of hormonal patterns, which we have used in previous studies [53], using *R*-software (*R* Foundation for Statistical Computing, Vienna, Austria). The specific statistical methods involve creating best-fit distributions for wave patterns of the hormones using the mean square of residuals as the loss function, with the goal to minimize the loss function to improve the fit of the distribution based on the density of the hormone wave patterns in the population; this specific method has helped to identify distinct hormone patterns that may represent different physiologic mechanisms, but it must be emphasized that these are hypothesis-generating rather than primary endpoints of this proposal.

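### The 80% power stated for 150 cycles is not quite that of the planned Spearman test, which has about 76% or 79% depending on what the effect size of 0.2 measures

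*Protocol article*

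**What the plan says.** Section 2.4 of the protocol article takes its size from earlier ultrasound validation work that "targeted 50 participants over 3 cycles, for a total of 150 menstrual cycles", and then supports it with a calculation: "This calculation was done with G*Power 3.1, with an effect size of 0.2, alpha 0.05, and power of 80" per cent. The next sentence gives the test family and the direction: "This calculation is valid for correlation statistics with an a priori power analysis with one tail". The section names no coefficient and does not say on which scale the 0.2 is measured. It foresees some loss of cycles: "Oversampling up to 60 participants may be required to ensure that we have 150 cycles for analysis". The same size is then adopted for the PCOS and athlete groups.

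Section 3.1 names the test to which the power statement applies: "The main analysis in this sample (for which it is powered) will be to correlate (with Spearman’s correlation coefficients) the day of ovulation" with the day of peak LH on the monitor and with the day of progesterone elevation.

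**The concern.** Read together, the two sections say that a one-tailed Spearman test on 150 cycles has 80% power at 0.2. Spearman's coefficient uses ranks, so for bivariate-normal data its test has somewhat less power than Pearson's. Its population value is also slightly smaller than the Pearson correlation of the same data. A sample size solved for another correlation test therefore does not carry over unchanged, and the general statement that the calculation is valid for correlation statistics is too broad.

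What is at stake is the accuracy of one printed figure. It is the power of the only analysis described as powered, and it applies to all three groups. The point does not depend on the 0.5-day claim in the same paragraph or on the repeated cycles within each woman: it holds even for 150 fully independent cycles.

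**Working it through.** **Inputs.** Section 2.4 gives effect size 0.2, alpha 0.05, one tail, power 80% and n = 150 cycles. Section 3.1 gives the test, Spearman. Two assumptions are added because the article does not give them: the cycles are independent, and the two day variables are bivariate normal without ties.

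**Step 1: reproduce the plan's figure.** In the point-biserial (fixed-X) model the test statistic follows a noncentral t with n − 2 degrees of freedom and noncentrality δ = √(n r²/(1 − r²)).

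- At n = 150: δ = √(150 × 0.04/0.96) = √6.25 = 2.50, with 148 degrees of freedom. Power is 80.06%.
- At n = 149: power is 79.8%.

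So 150 is exactly the smallest n that reaches 80% in this model.

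**Step 2: try other one-tailed calculations with 0.2 and alpha 0.05.**

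| Calculation | Power at 150 | n for 80% |
|---|---|---|
| Point-biserial, noncentral t | 80.06% | 150 |
| Pearson, exact bivariate normal | 79.5% | 153 |
| Pearson, Fisher z | 79.2% | 154 |
| One-sample or paired t, d = 0.2 | 78.6% | 156 |

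For Fisher z, atanh(0.2) = 0.2027. The required n is ((1.645 + 0.842)/0.2027)² + 3 = 153.4, rounded up to 154.

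**Step 3: Spearman if 0.2 is a Pearson correlation.** Under bivariate normality the population Spearman value is (6/π) × arcsin(0.2/2) = 0.191. Simulated one-tailed power, with 200,000 replicates per setting, was:

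- n = 150: 75.7%
- n = 167: 79.8%
- n = 169: 80.2%

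The simulated rejection rate under no correlation at n = 150 was 4.96% (100,000 replicates), so the test keeps its level. As a cross-check, Spearman's asymptotic relative efficiency to Pearson is 9/π² = 0.912. Then z = 0.2027 × √(147 × 0.912) − 1.645 = 0.702, which is 75.9% power. The required n is 3 + 150.4/0.912 = 168. Both routes give about 76% at 150 and about 169 cycles for 80%.

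**Step 4: Spearman if 0.2 is Spearman's own rho.** The corresponding Pearson value is 2 × sin(π × 0.2/6) = 0.209. Simulated one-tailed power was:

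- n = 150: 79.3%
- n = 153: 79.7%
- n = 155: 80.3%

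That is about 79% at 150 and about 155 cycles for 80%. The common large-sample variance 1.06/(n − 3) is harsher here (77.1% and 163 cycles). The simulation evaluates the test directly and is preferred.

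**Step 5: size of the gap.** 80 − 76 = 4 points on the Pearson reading and 80 − 79 = 1 point on the Spearman reading.

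**The case against.** The best defence is that the article never calls 0.2 a Pearson value. Since Section 3.1 describes the Spearman analysis as the powered one, the natural reading is that 0.2 is the Spearman coefficient to be detected. Power is then about 79%, close to rounding. This stands. A reader might infer flatly that the trial has 76% power and needs 169 cycles, but those figures hold only if 0.2 is a Pearson correlation of bivariate-normal data, which the article does not say.

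A reader might also infer from the exact match that the wrong G*Power routine was run. The match is good evidence, but it is an inference. The article names no routine, and 150 is also the 50 × 3 taken from precedent. Wherever the number came from, 80% is not Spearman's power at 150 on either reading.

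The practical objection is also fair. Section 1.4 expects the ultrasound day to be highly correlated with urinary hormones. In a simulation at 150 cycles, one-tailed Spearman power is 90% at a Pearson correlation of 0.25, 97% at 0.3 and effectively 100% at 0.5. The gap at 0.2 is unlikely to decide anything. A two-sided reading would give a much lower power, but Section 2.4 specifies one tail, so that figure does not bear on the plan.

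**Conclusion.** The point holds in a small, conditional form. The stated 80% at 150 cycles is the exact point-biserial result (80.06%). The Spearman test that Section 3.1 calls powered has about 76% if 0.2 is a Pearson correlation, or about 79% if 0.2 is Spearman's rho; 80% would need about 169 or about 155 cycles respectively. The shortfall is 1 to 4 points and is minor.

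These figures assume 150 independent cycles and bivariate-normal, untied data. The plan has three cycles per woman, and ovulation days are whole numbers, so the independence condition should be printed with any restated figure. A reader might conclude that the study is underpowered and must recruit more. The documents do not support that: the gap is small, its size depends on an unstated scale, and much stronger correlations are expected.

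**What to change.** In Section 2.4, state which coefficient the 0.2 refers to and restate the power for the planned test. For example: *With 150 independent cycles, the one-tailed Spearman test at alpha 0.05 has about 76% power if the underlying Pearson correlation is 0.2 (about 79% if Spearman's rho is 0.2).* Keep only the half that applies once the scale is fixed, and use the same statement for the PCOS and athlete groups, which share the size.

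This is a change of one sentence. The target of 150 cycles and the enrolment of up to 60 participants per group can stay as they are. The downside is that the printed power becomes slightly less favourable.

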### 2.5. Demographic and Clinical Surveys

The inclusion survey and consent will be completed on REDCap (Research Electronic Data Capture, www.project-redcap.org, accessed on 15 September 2022). If they meet the criteria, participants will review the Patient Information and Consent Form. After consenting via digital signature, they will be provided a link to enter demographic information within REDCap.

In addition to demographic data, a medical history questionnaire will be completed by each eligible participant directly in REDCap. The confidential (non-identifying) data is housed on the REDCap platform for the University of Calgary. Only investigators in this study will have access to the study data on REDCap.

Hormonal data from the Mira monitor will be entered directly into the Read Your Body App, developed by a non-profit women’s health initiative in the United Kingdom [46], and then sent directly to REDCap (see Figure 3). All data collection and analysis will follow provincial [47,48] and federal [49] privacy legislation. No biospecimens will be saved as part of this study (specimens are all home-based urine sampling with disposable test sticks).

### 2.6. Mira Monitor Testing Protocol

Participants will be given a Mira fertility monitor and enough test wands for three menstrual cycles. The Read Your Body (RYB) App (Figure 3) will need to be downloaded onto participants’ smartphones, and the participants will set up a personal accounts which the investigators will not have access to. The app developers have no way of accessing personally identifying details, nor menstrual cycle data, from the RYB app. Users of the app will have 3–4 months of free use of the App during the study. Email addresses and any other personally identifying details will not be collected by the app team nor by the research team through the app. Over the three menstrual cycles, participants will test daily first-morning urine (using an initial stream catch in a clean cup) with the Mira monitor for menstrual cycle hormones (FSH, E_1_3G, LH, and PDG) as well as take their temperature with a basal body thermometer. Data from the Mira monitor, menstrual cycle observations and bleeding patterns will be entered manually into the Read Your Body App. Bleeding patterns will be recorded with the bleeding score integrated in the app (see Section 2.7), and other observations (intercourse patterns, mucus secretions, open text observations) are also optionally available for manual entry in the app. The app provides cycle summaries and visual graphs of cycle changes to help improve menstrual health literacy for the individual user.

### 2.7. Menstrual Bleeding Assessment

The bleeding score for this study will be based on the Mansfield–Voda–Jorgensen (MVJ) Menstrual Bleeding Scale [38]. This is a 1–6 score, to which we will add a category 0 for “no bleeding.” This score will be built into the RYB App with explanations for each score available for participants’ reference:

(0) No bleeding.

(1) Spotting, a drop or two of blood, not even requiring sanitary protection though you may prefer to use some.

(2) Very light bleeding (you would need to change the least absorbent tampon or pad one or two times per day, though you may prefer to change more frequently).

(3) Light bleeding (you would need to change a low or regular absorbency tampon or pad two or three times per day, though you may prefer to change more frequently).

(4) Moderate bleeding (you would need to change a regular absorbency tampon or pad every 3 to 4 h, though you may prefer to change more frequently).

(5) Heavy bleeding (you would need to change a high absorbency tampon or pad every 3 to 4 h, though you may prefer to change more frequently).

(6) Very heavy bleeding or gushing (protection hardly works at all; you would need to change the highest absorbency tampon or pad every hour or two).

### 2.8. Serum Hormone Measurement

Serum hormones (FSH, estrogen, LH, progesterone) will be measured in the follicular phase, around the time of ovulation, and in the luteal phase. Serum AMH will be collected once for each participant. These tests are collected in lithium heparin tubes and analyzed on an E801 Cobas Roche analyzer. For progesterone and estradiol, the serum assay will use the competition principle, and for FSH and LH, the serum assay will use the sandwich principle (similar to the urine tests described in Figure 3).

### 2.9. Ultrasound Protocol

Follicular tracking ultrasounds will be carried out on a single machine (Canon, Xario 200G [50], regularly serviced by Canon technicians) in one clinic in Calgary with approximately 6–8 ultrasounds per cycle, for a total of 18–24 ultrasounds over the course of the three cycles of study. The endovaginal ultrasound protocol will be supervised by a radiologist and has been developed based on previous follicular-tracking ultrasound studies [51,52]. Ultrasound scans will be carried out by trained ultrasound technologists with endovaginal follicle-tracking experience. Processing and high-level disinfection of the ultrasound probes will be in compliance with the protocols recommended by the ultrasound probe manufacturer (Canon) and the College of Physicians and Surgeons as used by radiology clinics. A radiologist will be involved in identifying pitfalls and updating protocols throughout the project. The ultrasound machine and hard copies of ultrasound probe-processing tracking will be kept in a locked office. The ultrasound scans are kept locally on the ultrasound hard drive and will not be uploaded to any other system.

## 3. Results (Planned)

### 3.1. Data Analysis

Datasets will be analyzed using SPSS version 29 (IBM, Chicago, IL, USA) and charts prepared using SPSS or Excel (Microsoft, Redmond, WA, USA). Descriptive statistics will be used to determine the means, standard deviations (SD), and 95% confidence intervals (CI) of the menstrual cycle parameters, i.e., cycle length, day of ovulation, length of the follicular phase and the luteal phase, menstrual bleeding scores, and duration. The ultrasound-defined day of ovulation (US-DO) will be considered day 0 as a reference for days leading up to and after ovulation. The main analysis in this sample (for which it is powered) will be to correlate (with Spearman’s correlation coefficients) the day of ovulation with peak levels of LH on the Mira monitor, as well as with the day of progesterone elevation, to confirm ovulation. Sensitivity and specificity analyses of each hormone in relation to the US-DO will be calculated.

Secondary exploratory data analyses (not considered in the power calculations) will include daily average hormone values from the Mira monitor referenced to day 0 (US-DO), average hormone values, 95% confidence individuals on days leading up to ovulation (days −5, −4, −3, −2, −1, etc.), and after ovulation (days +1, +2, +3, +4, +5 etc.) from cycle day 6 until the end of the cycle. Daily means, SDs, and CIs of hormone values across the study sample will be used to describe the variability in the population, as was done in the pilot study [34], and individual (personalized) hormone patterns will also be considered as we have presented in previous studies [51]. Day-to-day hormone variability will require complex modelling of hormonal patterns, which we have used in previous studies [53], using *R*-software (*R* Foundation for Statistical Computing, Vienna, Austria). The specific statistical methods involve creating best-fit distributions for wave patterns of the hormones using the mean square of residuals as the loss function, with the goal to minimize the loss function to improve the fit of the distribution based on the density of the hormone wave patterns in the population; this specific method has helped to identify distinct hormone patterns that may represent different physiologic mechanisms, but it must be emphasized that these are hypothesis-generating rather than primary endpoints of this proposal.

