**Figure 3 medicina-59-01513-f003:**
[figure not shown]
Data collection process for the study. Mira monitor urine results and other menstrual cycle observations are recorded in the Read Your Body (RYB) App. Users collect, control, and own the data they collect. RYB data is stored locally. Participants can then voluntarily send their anonymous data to a REDCap research database. Component figures used with permission.

**Table 1 medicina-59-01513-t001:** Inclusion and exclusion criteria for regular cycles.

Inclusion Criteria	Exclusion Criteria
Regularly menstruating participants aged 18–45 Consistent cycle lengths between 24–38 days Knowledge of previous 3 cycle lengths Negative pregnancy test at the beginning and at the end of each cycle Able to travel to clinic in Calgary for regular ultrasounds during the study period	Anovulation in the last 3 cycles Currently, or in the previous 3 months, on medications that are known to impair or stimulate ovulation (e.g., oral contraceptives, ovulation stimulants, etc.) Known conditions that impair ovulation or fertility: ▪ polycystic ovarian syndrome ▪ endometriosis ▪ pelvic inflammatory disease in the last year ▪ pituitary adenoma ▪ breastfeeding Previous surgeries impacting the menstrual cycle: ▪ hysterectomy ▪ bilateral oophorectomy Currently pregnant

**Table 2 medicina-59-01513-t002:** Inclusion and exclusion criteria for oligomenorrheic cycles.

Inclusion Criteria	Exclusion Criteria
Participants aged 18–45 With a clinical diagnosis of PCOS (Rotterdam criteria [45] to include oligomenorrheic cycles and one of either polycystic ovaries or signs of excess androgens) OR Oligomenorrheic athletes	Currently, or in the previous 3 months, on medications that are known to impair or stimulate ovulation (e.g., oral contraceptives, ovulation stimulants, etc.) Known conditions that impair ovulation or fertility: ▪ pelvic inflammatory disease in the last year ▪ pituitary adenoma ▪ breastfeeding Previous surgeries impacting the menstrual cycle: ▪ hysterectomy ▪ bilateral oophorectomy Currently pregnant

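### The powered main analysis tests the LH-peak correlation against zero, but a monitor reading pure noise would not give zero, because testing stops when the cycle ends

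*Protocol article*

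**What the plan says.** Section 3.1 identifies the analysis for which the sample is powered. It "will be to correlate (with Spearman’s correlation coefficients) the day of ovulation with peak levels of LH on the Mira monitor". A second arm of the same analysis uses PDG: US-DO, the ultrasound-defined day of ovulation that serves as day 0, is also to be correlated "as well as with the day of progesterone elevation, to confirm ovulation".

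The only inference attached to this is in section 2.4: "This calculation was done with G*Power 3.1, with an effect size of 0.2, alpha 0.05, and power of 80" per cent. The text then adds, on the type of test, "This calculation is valid for correlation statistics with an a priori power analysis with one tail". The target comes from earlier work that "targeted 50 participants over 3 cycles, for a total of 150 menstrual cycles", and the PCOS and athlete groups use the same size.

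On the sampling window, section 2.6 says: "Over the three menstrual cycles, participants will test daily first-morning urine". The legend to Figure 1 defines the luteal phase as running from ovulation to the end of the cycle.

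For the main analysis the article gives no null value other than the implied zero, no measure of agreement in days and no success threshold. Sensitivity and specificity against US-DO are also planned, without a threshold.

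**The concern.** The hypothesis in section 2.1 is that Mira LH predicts and PDG confirms the day of ovulation. A test of rho = 0 speaks to that only if a monitor carrying no information would give rho = 0.

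For the day of the LH peak it would not. The peak day and US-DO are both counted from the start of the cycle, and the search for the peak runs to the end of the same cycle. A longer cycle widens the range in which a random peak can fall, and it also usually means later ovulation. The two days therefore move together with no hormonal signal at all.

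This is separate from a constant day offset and from the clustering of cycles within women. What is at stake is whether a significant coefficient can be offered as external validation, above all in the two irregular groups, where cycle length varies most.

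**Working it through.** **Inputs from the article.** Effect size 0.2, alpha 0.05, power 80%, one tail, 150 cycles (2.4). Daily urine testing over each cycle (2.6). Regular cycles of 24–38 days (Table 1). Cycle length = ovulation day + luteal length (Figure 1 legend). Secondary hormone series from cycle day 6 to cycle end (3.1).

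**Assumptions (the article gives no means or SDs).** Regular cycles: mean length 29 days, SD 2–4 days before truncation to 24–38. Luteal phase: mean 14 days, SD 1–2.5 days. Irregular cycles: mean 40–45 days, SD 6–12 days, luteal SD 2–3 days. Noise peak: uniform from the first test day (1 or 6) to the last day of the cycle.

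**1. The article's own figure.** A one-tailed t test of r = 0.2 against zero gives N = 150 (power 80.06%). By Fisher z, n = (2.4865/0.20273)² + 3 = 153.4, and power at 150 is Φ(0.20273 × √147 − 1.645) = Φ(0.813) = 79.2%. Two-tailed versions need 191–194. The null behind the design is therefore rho = 0. At n = 150 the smallest significant coefficient is 1.655/√(148 + 1.655²) = 0.135.

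**2. The mechanism in one case.** Let L be cycle length, O = L − luteal length, and X a noise day uniform on s to L. Then E(X|L) = (s + L)/2. If luteal length is independent of L, Cov(X, O) = ½Var(L). Also Var(X) = Var(L)/4 + E[(L − s + 1)² − 1]/12.

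Take mean 29, SD 2, s = 6 and luteal SD 1.5:
- Cov(X, O) = ½ × 4 = 2
- Var(X) = 1 + (24² + 4 − 1)/12 = 49.25, so the SD is 7.02
- SD(O) = √(4 + 2.25) = 2.5
- Correlation = 2/(7.02 × 2.5) = 0.114

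The simulated mean Spearman coefficient is 0.102. Expected rejection is Φ(atanh(0.102) × √147 − 1.645) = Φ(−0.40) = 34%; simulation gives 35%.

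**3. Simulation, 4,000 trials of 150 cycles, one-tailed 0.05, pure-noise peak day.**

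| Assumed cycles | Mean noise rho | Rejection |
|---|---|---|
| Regular, SD 2 d | 0.07–0.12 | 20–41% |
| Regular, SD 3 d | 0.11–0.16 | 38–62% |
| Regular, SD 4 d | 0.14–0.19 | 53–76% |
| Regular, uniform 24–38 d | 0.19–0.24 | 77–90% |
| Irregular, mean 40–45, SD 6–12 d | 0.20–0.35 | 78–99.8% |
| Control: regular, SD 3 d, window closed on day 24 for all | 0.00 | 4.3–4.9% |

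The control isolates the cause: with a common end to the window, the error returns to nominal. Correlation of cycle lengths within women (ICC 0.5) barely matters: 41–51% against 42–54% at SD 3, luteal SD 2. A parallel set with lengths clipped rather than redrawn and ICC near 0.35 reached 80% at SD 4.

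**4. Progesterone day.** If elevation is a first crossing that noise triggers with probability 10% per day, rejection is about 5–7%, essentially nominal. At 5% per day, with cycles lacking a crossing set to cycle end, it is 14–38%. The result depends on a rule that the article does not give.

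**5. The alternatives.** Partial Spearman given cycle length returns noise to 4–7% and keeps about 100% power for a monitor with 1-day error SD. Its coefficient is 0.81–0.88, against a raw 0.92–0.99. An assumed 1-day ultrasound error lowers it to 0.67–0.77.

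Agreement in days also separates the cases. In a day 6–29 window, noise falls within ±1 day of US-DO in 3/24 = 12.5% of cycles. A monitor with 1-day error centred on its target does so in P(|Z| < 1.5) = 87%, or in P(−0.5 < Z < 2.5) = 69% if it leads by one day and the lead is not allowed for.

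**The case against.** The best defence is that no passage says p < 0.05 against zero amounts to validation. The coefficient itself will be reported, with sensitivity, specificity and hormone profiles aligned to US-DO. A good monitor would show rho of 0.92 or more and a visible LH peak near day 0, whereas noise would show 0.1–0.2 and a flat profile. This stands: a careful reader of the full output would not be misled. It does not rescue the powered inference, which sets no such bar and is met by an observed coefficient of 0.135.

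Section 2.4 also mentions detecting differences of 0.5 days, which is nearer to agreement. Section 3.1, however, names correlation as the powered analysis.

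Four stronger readings are tempting and should not be drawn:
- **That noise usually passes.** In regular cycles with SD 2 days it passes in a minority of trials. Above half needs an SD of about 3 days or more, mostly with testing from day 6. The irregular-group rates rest on assumed spreads.
- **That the progesterone analysis fails equally.** Under a first-crossing rule it may not fail at all.
- **That a calendar guess from past cycle lengths would always pass.** In simulation this gave 95–100% at within-woman ICC 0.3–0.4 but only 44–76% at 0.1–0.2.
- **That a partial correlation is a complete remedy.** It cannot see a constant offset, so a monitor that is always several days early would pass. It also conditions on a length known only after ovulation, and it removes much of the true variation between cycles.

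**Conclusion.** The point holds for the day of the LH peak. The null implied by 2.4 and 3.1 is not that of an uninformative monitor, and the error rate for a validity claim is several times the nominal 5%: about 20–40% in regular cycles at SD 2 days, about 40–80% at 3–4 days, and about 80–100% in irregular cycles. The direction follows from the article's own sampling window and definitions; the sizes rest on assumed SDs and on a uniformly placed noise peak. Section 3.1 refers to peak levels; if the level rather than the day is meant, noise still rejects in 20–26% (SD 3, luteal SD 2). For the progesterone day the inflation is undetermined and may be negligible. Rejecting rho = 0 shows a non-zero correlation and does not show that the monitor identifies the day of ovulation.

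**What to change.** **Section 3.1.** Write 'day of peak LH'. Base the validity claim on agreement in days between the Mira day and US-DO: the proportion of cycles within ±1 day with a 95% confidence interval, or the mean difference with limits of agreement. State the target day, so that any expected LH lead is handled in advance. If a correlation test is kept, make it a partial Spearman correlation given the length of that cycle.

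**Benchmark.** Table 1 requires "Knowledge of previous 3 cycle lengths", so for Group 1 the error of a calendar-predicted day can be reported beside the Mira error. Table 2 has no such criterion, so this should not be promised for the PCOS and athlete groups unless those lengths are collected.

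**Section 2.4.** State that 150 cycles at r = 0.2 against zero power detection of a non-zero correlation, not validity of the monitor.

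**Cost.** Wording only; no extra visits or participants. If cycles were independent, 150 would give a proportion to within 1.96 × √(0.25/150) = 8 percentage points at worst; the interval should allow for three cycles per woman. The price of the partial coefficient is a lower headline figure: about 0.8–0.9, or 0.67–0.77 with an assumed 1-day ultrasound error.
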